### Cohort Procedures

Participants will complete a computer-assisted self-interview (CASI) every 3 months while in the study. Surveys will be hosted on REDCap. EPICC surveys will be distributed through emails and links available within the study app. mChoice surveys will be completed at study sites on a tablet. The surveys will address various topics related to PrEP care engagement, PrEP usage, and PrEP adherence, as well as sociodemographics and risk factors related to PrEP adherence (Table S1 in Multimedia Appendix 1) [7,28-38].

EPICC project participants will complete a home-based DBS collection kit every 6 months while in the study to assess for levels of tenofovir-diphosphate (TFV-DP) and emtricitabine-triphosphate (FTC-TP). Additionally, EPICC project participants can attend an optional virtual onboarding visit with a member of the study team to review key features of the study app and DBS collection instructions. mChoice project participants who report using PrEP containing TFV and FTC will provide a urine sample of 15-30 mL at each visit to measure adherence. After the visit, the staff will use the urine sample for a rapid strip test to interpret adherence results. The staff will upload a picture of the test results to REDCap to send to the lab so that they can perform quality control checks. Participants’ urine samples will be used for 2 separate tests: one that measures TFV levels and another that measures FTC levels. Throughout the study period, participants (EPICC and mChoice) will be asked to track their PrEP adherence and sexual behavior in study mobile applications. Electronic health record (EHR) data (EPICC and mChoice Studies) will be collected every 6 months during the study period; variables will include PrEP prescription information, HIV testing, sexually transmitted infection (STI) testing, and results. Clinic site staff will complete medical record abstraction (MRA) using participants’ EHRs every 6 months while in the study. MRA will collect information about PrEP prescriptions, STI testing and results, and HIV testing and results. Table S1 in Multimedia Appendix 1 includes cohort measures.

A subset of EPICC project participants will also complete exit interviews. Questions will focus on understanding factors that influenced participants’ selection of PrEP regimens, changes, or discontinuations; perceptions of the counseling they received by providers at PrEP initiation and follow-up; and the receipt of tools or materials that influenced their choice and feasibility/acceptability of the HMP app. The mChoice project team will similarly conduct in-depth interviews with a subset of participants following completion of the intervention to explore experiences with PrEP, reasons for PrEP choices, and impressions of the mChoice intervention.

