### Primary Outcome Measures

The primary outcome for provider training is PrEP familiarity, PrEP beliefs, and intentions to use PrEP measured at pre- and posttraining. The primary outcome for the cohort is PrEP adherence. For the EPICC project, adherence outcomes will be measured by using blood and will be tailored for oral PrEP modality (daily or 2-1-1) and categorized as protective (1) or not protective (0). The protective level of PrEP in the blood is defined as ≥4 doses taken per week, and the not-protective level is defined as <4 doses taken per week. Adherence outcomes for participants on CAB-LA will be determined by the timely administration of injections. The timely administration of the second injection is defined as within +/–1 week of the target date and within +/–2 weeks of the target date for subsequent injections. For the mChoice project, adherence outcomes, as measured by using urine, will be assessed by testing TFV and FTC levels in urine specimens collected from participants who report daily use of PrEP containing TFV and FTC. The mChoice project will also measure adherence by electronic medication monitoring via the CleverCap device, EHR data, and self-report.

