#### The mChoice Project

##### Sample Size and Power Calculations

Sample size estimation was based on the number of individuals required in order to detect an odds ratio of 1.7 or greater, based on a previous intervention study [42], in the primary outcome measures (PrEP adherence and persistence) before and after the intervention. We used a GLMM [43] with 80% power and a 2-sided test of .05 significance. We estimated the power and sample size by simulating responses based on the following assumptions: 20% attrition postintervention follow-up, an intraclass correlation coefficient of 0.2 across sites, and correlations in the range of 0.3-0.6 of participants’ outcomes at different time points [43]. With these conditions, a sample size of 400 was needed [43].

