### Limitations

This research is limited in its design as a cohort study and not a randomized controlled trial. However, early work to harmonize measures and outcomes across the 2 projects is expected to allow for informative descriptions and the possibility for both pooled and separate analyses, as well as comparison across the entire study. Although multiple study sites across the United States are included, PrEP Choice is not a nationally representative study and results will not be generalizable.

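### mChoice self-report and urine both require a study-site visit, so people who stop PrEP or leave the clinic may be under-represented in those two measures

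*Protocol article*

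**What the plan says.** All of the following is in the protocol article.

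- **Surveys (Cohort Procedures).** Both projects host three-monthly surveys on REDCap. For mChoice, "mChoice surveys will be completed at study sites on a tablet". For EPICC, "EPICC surveys will be distributed through emails and links available within the study app".
- **Drug levels (Cohort Procedures; Primary Outcome Measures).** EPICC uses home blood-spot kits. In mChoice, "mChoice project participants who report using PrEP containing TFV and FTC will provide a urine sample of 15-30 mL at each visit". The outcome section describes a narrower group: "urine specimens collected from participants who report daily use of PrEP containing TFV and FTC".
- **Records (Cohort Procedures).** One sentence has health-record data, including prescriptions, collected six-monthly over the study period. The next says "Clinic site staff will complete medical record abstraction (MRA) using participants’ EHRs every 6 months while in the study". Both cover both projects.
- **Other mChoice sources.** Primary Outcome Measures adds the CleverCap device, health records and self-report as adherence measures. Cohort Procedures adds tracking in the app.
- **Analysis (The mChoice Project, Primary Outcome).** A GLMM compares outcomes before and after the intervention, controlling for baseline values. There is no comparison group.
- **Sample size (The mChoice Project).** The plan assumes "20% attrition postintervention follow-up" and targets an odds ratio of at least 1.7 in adherence and persistence.
- **Use across projects (Limitations).** Harmonized measures are expected to allow "the possibility for both pooled and separate analyses, as well as comparison across the entire study".

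**The concern.** Everyone enters with an active prescription and in care at a study site (Longitudinal Cohort). Those who later stop PrEP, or move their care, have less reason to return to that site. In mChoice, a missed visit costs the survey and the urine sample together. The survey is the measure that could have shown that the person had stopped.

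Without a control group, no second arm shares the same loss. If stoppers are lost more often than users, the follow-up rate among those observed rises without any change in behaviour, and the before-after contrast reads this as benefit.

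The mode of follow-up also differs by project. An EPICC participant who has left the clinic can still answer a link. A difference between projects could therefore partly reflect who remained observable.

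**Working it through.** **1. The plan's own figure.** The stated mChoice sample size is 400. It can be neither confirmed nor refuted, because the article gives no baseline rate. A paired approximation that ignores the site intraclass correlation is

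n = (1.96 + 0.84)² × [1/(p₁q₁) + 1/(p₂q₂) − 2ρ/√(p₁q₁p₂q₂)] / (ln 1.7)², then divided by 0.80 for attrition.

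At ρ = 0.3 and 0.6 (the ends of the plan's range) it gives:

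| Assumed baseline rate | N at ρ = 0.3 | N at ρ = 0.6 |
|---|---|---|
| 20% | 272 | 157 |
| 50% | 203 | 117 |
| 90% | 703 | 413 |

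So 400 lies within the range of possible inputs. The present point does not depend on it.

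**2. Which mChoice measures need a visit.**

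| Source | Visit stated? | Limit |
|---|---|---|
| Survey self-report | Yes, on-site tablet | Lost with the visit |
| Urine TFV and FTC | Yes, at each visit | Only from those reporting use (daily use, in the outcome section) |
| CleverCap | No | A pill bottle: does not measure injections; an unopened bottle may mean stopping PrEP or abandoning the device |
| App tracking | No | Needs continued engagement |
| Health records | No | Site records may miss care elsewhere; a prescription is not adherence |

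A participant who attends but reports having stopped also gives no urine, so the survey is the main direct measure of stopping. Substance use, a secondary mChoice outcome, is not among the record variables listed in Cohort Procedures, so the on-site survey is its only evident source.

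**3. Size at the plan's 20% attrition.** Assume true PrEP use at follow-up of 60% (the documents give no figure). Let r₁ be the share of users retained and r₀ the share of stoppers retained.

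0.80 = 0.6 r₁ + 0.4 r₀; observed use = 0.6 r₁ / 0.80; inflation of the odds = r₁ / r₀.

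| r₁ (assumed) | r₀ | Observed use | Excess (points) | Odds inflated by |
|---|---|---|---|---|
| 0.80 | 0.80 | 60.0% | 0 | 1.00 |
| 0.85 | 0.725 | 63.8% | 3.8 | 1.17 |
| 0.90 | 0.65 | 67.5% | 7.5 | 1.38 |
| 0.95 | 0.575 | 71.3% | 11.3 | 1.65 |

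**4. A second set of assumptions.** Suppose true adherence p is 50% before and after (no change), attrition a is 0.20, and adherence among those lost is d. Observed = (p − a·d)/(1 − a).

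- d = 0: 0.50/0.80 = 62.5%, a spurious odds ratio of 1.67 against the whole-cohort baseline.
- d = 0.25: 0.45/0.80 = 56.3%, a spurious odds ratio of 1.29.
- d = 0.50: 50%, no bias.

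Against the completers' own baseline, simulation with ρ from 0.6 to 0.3 gives smaller values: about 1.23 to 1.44 for d = 0 and 1.10 to 1.19 for d = 0.25.

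Steps 3 and 4 describe raw proportions among those observed. They are not estimates from the planned GLMM, and they give no credit to CleverCap, app or record data.

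**The case against.** A reader might infer that stoppers vanish from the mChoice outcomes altogether, that record abstraction ends once they disengage, and that adherence will be overstated by some 4 to 11 points. The documents do not support that reading.

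- **Other sources exist.** CleverCap, app tracking and health records have no stated visit requirement, and regimen-change dates come from the records (The mChoice Project, Secondary Outcomes). This stands. Step 2 shows only that these sources are incomplete.
- **The abstraction window is not clearly limited.** The words "EHRs every 6 months while in the study" follow a sentence that gives the study period as the window. The wording applies equally to EPICC, and nothing says that stopping PrEP or missing a visit ends participation. What remains is a need to reconcile the two sentences.
- **Payments encourage attendance.** mChoice pays per survey, rising from US $40 at baseline to US $80 at 18 months (Ethical Considerations), whatever the PrEP use. This should reduce loss, though as described the payment still depends on completing a survey that is taken on site.
- **The bias is conditional.** It needs those lost to be less adherent, which the plan's 20% does not say. A GLMM using all available data reduces bias where loss depends on observed values. It cannot reliably repair the case in which someone stops between visits and never returns, because the last observed value is then still on PrEP.
- **Cross-project analysis is only a possibility.** Limitations offers it and does not commit to it.
- **The article is condensed.** Rules for missed visits and missing data may sit in the full protocol or SAP, and their absence here is no fault. The point rests on the survey procedure that is stated.

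**Conclusion.** The point holds in limited form. mChoice self-report and urine depend on site attendance where EPICC's equivalents do not, so people who stop PrEP or leave the clinic may be under-represented in those two measures. In an uncontrolled before-after analysis, such loss would bias observed adherence and persistence upward, and it could confound a cross-project comparison.

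The size is illustrative: 3.8 to 11.3 points at 20% attrition, an assumed 60% true use and assumed retention of 85% to 95% of users. It is zero if loss is unrelated to PrEP use. At the upper end, the inflation of the odds (1.65) approaches the odds ratio of 1.7 for which the study is sized, which is enough to justify an inexpensive safeguard. It does not show that the mChoice result will be biased.

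**What to change.** 1. Keep the on-site tablet as the default. When an mChoice participant misses a visit, send the existing REDCap survey by email or app link with the same payment. The means are in place: EPICC already distributes this way, and daily smartphone access is an eligibility criterion.
2. Reconcile the two sentences on record collection in Cohort Procedures, so that abstraction runs to the planned end of follow-up for everyone who has not withdrawn consent to it.
3. Use those records to support classification of PrEP status when the survey is missing. They should not settle it alone, because care moved elsewhere can look like stopping.

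The costs are a small difference between tablet and remote responses, no urine from remote responders, and a short protocol and consent amendment. Results reports 18 mChoice participants enrolled by October 2024. Early adoption matters, because surveys missed now cannot be recovered later.

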### Postcohort Provider Focus Group Discussions and Interviews

After the cohort is completed, the EPICC project team will conduct 6 virtual focus groups with PrEP providers, clinic staff, and study staff. The purpose of the focus groups will be to gather feedback on overall perceptions of the barriers and facilitators to education tool implementation within their clinical site. Prior to participating in the focus groups, participants will complete a survey that will collect their demographics, whether the provider can prescribe PrEP, and how long the provider has worked at their current clinic.

The mChoice project team will conduct in-depth interviews with participating providers following completion of the PrEP training modules and assessments. The research staff will ask participants about the implementation of the mChoice intervention, any long-term effects of the intervention, opinions of the provider training modules, and recommendations for future implementation of the mChoice intervention.

### Primary Outcome Measures

The primary outcome for provider training is PrEP familiarity, PrEP beliefs, and intentions to use PrEP measured at pre- and posttraining. The primary outcome for the cohort is PrEP adherence. For the EPICC project, adherence outcomes will be measured by using blood and will be tailored for oral PrEP modality (daily or 2-1-1) and categorized as protective (1) or not protective (0). The protective level of PrEP in the blood is defined as ≥4 doses taken per week, and the not-protective level is defined as <4 doses taken per week. Adherence outcomes for participants on CAB-LA will be determined by the timely administration of injections. The timely administration of the second injection is defined as within +/–1 week of the target date and within +/–2 weeks of the target date for subsequent injections. For the mChoice project, adherence outcomes, as measured by using urine, will be assessed by testing TFV and FTC levels in urine specimens collected from participants who report daily use of PrEP containing TFV and FTC. The mChoice project will also measure adherence by electronic medication monitoring via the CleverCap device, EHR data, and self-report.

### Secondary Outcome Measures

Secondary outcomes for provider training include the feasibility and acceptability of implementing provider training and barriers and facilitators impacting the implementation of new PrEP modalities in clinical practice measured through participant responses during the provider focus group discussions that will occur at the end of the cohort follow-up. The EPICC project cohort’s secondary outcome is persistence measures and will be based on (1) the participant’s self-report of currently taking PrEP (daily or 2-1-1) or having received the last shot of CAB-LA and (2) the participant having an active prescription for PrEP based on study records or drug levels associated with use within a 1-month window at 6 months, 12 months, and 18 months postenrollment. mChoice secondary outcomes will consist of sexual risk behaviors, HIV status, substance use, and outcomes by the initial PrEP regimen, as reported through follow-up assessments and EHR data.

### Statistical Analysis

Specific statistical analyses will be performed for the different projects. Next, we describe the EPICC and mChoice project analysis plans separately.

#### The EPICC Project

##### Sample Size and Power Calculations

The sample size for this study was determined based on feasibility after considering the intended analyses and multiple parameter estimates. With 400 participants, the minimum detectable difference in the PrEP adherence and persistence rates was 5.6%, assuming 15% loss to follow-up and a reference rate of 20%, at 0.80 power with a 1-sided test and 0.05 type I error. For baseline to postintervention analyses, simulation-based results indicated the minimum detectable difference from a baseline rate of 20% was approximately 9% (odds ratio 1.6), assuming again 15% loss to follow-up, at 0.80 power with a 1-sided test and 0.05 type I error [39].

##### Analysis Plan

Baseline participant characteristics will be described for the entire sample and disaggregated by regimen, site/region, ethnicity, level of HIV risk perception, substance use, PrEP experience (naive vs familiar), partner relationship status, and the other variables of interest included in Table S1 in Multimedia Appendix 1.

To determine any differences in discontinuation and nonadherence, we will use Cox proportional hazards to analyze (1) time to first discontinuation and (2) time to first nonadherence by regimen using PrEP adherence measures. To incorporate observations after the first discontinuation or after the first nonadherence, including allowing for the possibility of restarting on PrEP after discontinuation and for periods of nonadherence followed by a period of adherence, we will use a multilevel survival model by including a frailty term in the model to allow analysis of recurrent events [40]. We will follow the same analytic strategy for other dichotomous primary and secondary effectiveness and implementation outcomes. For the composite measure of number of prescriptions (primary implementation outcome), we will fit a multilevel linear or a generalized linear regression model, again using all the time point data available to assess the strength of the associations between the composite measure for the number of prescriptions and the predictor variables. To examine the trajectories of regimens, we will use generalized linear mixed models (GLMMs) and a survival model to assess the time to each regimen switch.

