### Provider Training

Each project will enroll participants for both provider training and the cohort from unique study sites. Figure 3 includes a map of each project’s enrollment sites.

The EPICC project team developed online PrEP training modules to educate providers on currently available PrEP options and how to engage clients in open discussions around sexual health and PrEP options. The goal of these open discussions between providers and clients is to encourage shared decision-making on PrEP options. The flexible and interactive modules were created using the Easygenerator online authoring tool, which allows learners to complete their assigned courses over multiple sessions at any time. The interactive features used throughout the modules are designed to keep providers engaged. Some of these features include checks for understanding, embedded videos, and links to external content. Each module also contains at least 1 case-based scenario. These scenarios are based on real-world interactions that study team providers experience during interactions with clients.

The EPICC project team developed these modules using a variety of content sources, including CDC-produced guidelines and materials, research papers, and expert guidance. In addition to modules covering PrEP regimens, we also included modules on the need for PrEP, PrEP screening and startup, postexposure prophylaxis (PEP), and PrEP adherence and persistence. The modules were refined to their final form through an iterative feedback process with subject matter experts within the EPICC project team. Both EPICC and mChoice project teams will use these modules in their respective provider training. Table 1 lists the titles and brief descriptions of each module.

Figure 4 includes screenshots of content within the modules that highlight interactive elements used throughout the course. The video image shown is from “Let’s Talk About Sexual Health” [19] produced by the CDC and BeSmartBeWell.com.

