##### Secondary Outcomes

Similar GLMMs will be used for analyzing secondary outcomes. We will conduct a multigroup comparison in pre- and postintervention differences (the difference-in-difference analysis) using a GLMM by adding the group variable and the group × intervention status interaction (pre- and postintervention) in the GLMM described before. Because the PrEP regimen cannot be randomized, we will use the propensity score method [45] to reduce the between-group bias. We will also examine factors that are associated with the length of time that participants take to change their regimens or associated with the instantaneous rate of change of regimen. Since we will know the date of change of the PrEP regimen (from the EHR data), we will apply a Cox proportion hazard ratio model with time-varying covariates (eg, sexual activity, insurance, side effect) to examine the time to change the regimen.

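### EPICC's comparison of discontinuation and nonadherence by regimen names no control for self-selection, although the same article plans a propensity score for mChoice regimen groups

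*Protocol article*

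**What the plan says.** Under Statistical Analysis, The EPICC Project, Analysis Plan, the purpose and model are: "To determine any differences in discontinuation and nonadherence, we will use Cox proportional hazards". The endpoints and grouping follow: "to analyze (1) time to first discontinuation and (2) time to first nonadherence by regimen". Later events are brought in "by including a frailty term in the model to allow analysis of recurrent events". The section then extends the same strategy to the other dichotomous primary and secondary outcomes.

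The plausible confounders appear in that section as baseline characteristics to be tabulated: "Baseline participant characteristics will be described for the entire sample and disaggregated by regimen, site/region, ethnicity, level of HIV risk perception, substance use", with PrEP experience and relationship status later in the same list. Predictors are mentioned for a different model, the one relating "the composite measure for the number of prescriptions and the predictor variables".

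Regimen is not allocated. Provider Training says the discussions with clients are meant to "encourage shared decision-making on PrEP options". Longitudinal Cohort admits people newly prescribed PrEP as well as people refilling it. Limitations acknowledges that this is a cohort without randomization.

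For the sister project, The mChoice Project, Secondary Outcomes says: "Because the PrEP regimen cannot be randomized, we will use the propensity score method", and gives reduction of between-group bias as the reason. The Statistical Analysis introduction says that the two projects' plans are described separately.

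**The concern.** A regimen contrast in a cohort where people choose their regimen compares different kinds of people as well as different regimens. Someone new to PrEP may differ from an established user both in the regimen chosen and in the chance of stopping. Site, risk perception and substance use can act in the same way. A frailty term allows for correlation among one person's repeated events; it does not balance the regimen groups.

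The contrast touches adherence, which is EPICC's primary cohort outcome, and discontinuation, which is close to its secondary outcome of persistence. If the published hazard ratio by regimen carries selection, a reader comparing regimens could draw a conclusion that the data do not support.

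**Working it through.** **1. The EPICC and mChoice texts side by side**

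| Item | EPICC, Analysis Plan | mChoice, Secondary Outcomes |
|---|---|---|
| Regimen contrast | Time to first discontinuation and first nonadherence; Cox, then frailty | Pre-post change compared between groups; GLMM with group-by-period interaction |
| Non-randomized regimen addressed? | Not in this section | Yes, explicitly |
| Adjustment named | None | Propensity score |
| Covariates in a Cox model | None named | Examples of time-varying covariates, for time to regimen change |

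The article therefore does report adjustment at this level of detail, for one of two cohorts that share eligibility criteria. Because the plans are described separately, the mChoice method cannot be assumed to apply to EPICC.

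**2. The plan's own figure**

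EPICC, Sample Size and Power Calculations gives a minimum detectable difference of 5.6 points (400 enrolled, 15% loss, reference rate 20%, power 0.80, one-sided 0.05).

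- Evaluable n = 400 × 0.85 = 340.
- One-sample test against a fixed 20%: power at 25.6% = Φ[(0.056 − 1.645·√(0.2·0.8/340)) / √(0.256·0.744/340)] = Φ[(0.056 − 0.0357)/0.0237] ≈ 0.80. The minimum detectable difference is 5.56 points, so the figure reproduces.
- Read as a two-regimen comparison of 340 people, one-sided, the minimum detectable difference would be 11.8 points at a 50:50 split and 19.6 points at 90:10.

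The stated figure thus fits a whole-cohort rate against a fixed reference, not a contrast by regimen. It says nothing for or against confounding.

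**3. How large could selection be?**

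The article gives no regimen shares, confounder prevalences or confounder hazard ratios, so every input here is assumed. Let the true regimen hazard ratio be 1. Let one binary confounder (for example, new to PrEP) multiply the hazard by h, and let its share be s₁ in one regimen group and s₂ in the other. The unadjusted ratio at the start of follow-up is

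(1 + s₁(h − 1)) / (1 + s₂(h − 1)).

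| s₁ vs s₂ | h = 1.5 | h = 2 | h = 3 |
|---|---|---|---|
| 50% vs 40% | 1.25/1.20 = 1.04 | 1.50/1.40 = 1.07 | 2.00/1.80 = 1.11 |
| 60% vs 30% | 1.30/1.15 = 1.13 | 1.60/1.30 = 1.23 | 2.20/1.60 = 1.38 |
| 70% vs 20% | 1.35/1.10 = 1.23 | 1.70/1.20 = 1.42 | 2.40/1.40 = 1.71 |

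The range is 1.04 to 1.71. If the imbalance runs the other way, the reciprocals apply: 1/1.04 = 0.96 to 1/1.71 = 0.58. The ratio drifts somewhat later as the higher-risk participants leave the risk set, so these are illustrations and not predictions.

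**4. What baseline adjustment would not solve**

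- The study expects participants to switch, stop and restart. A regimen fixed at baseline would assign later events to a drug no longer in use.
- Primary Outcome Measures defines EPICC adherence by drug level in blood for oral PrEP and by injection timing for CAB-LA. Covariates cannot turn those into the same event.

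**The case against.** The strongest reply is that this is a condensed article. The covariate list of a Cox model is commonly left to a fuller document, which is not shown, and silence is not a decision against adjustment. That stands as a limit on the wording: a reader might infer that EPICC has decided on unadjusted models, and the text does not say so. It does not dispose of the point. The article names the problem and a remedy for mChoice regimen groups, so their absence from the EPICC contrast is a gap at the article's own level of detail.

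A second reply is that the EPICC wording speaks only of differences, that the aims include describing real-world use, and that Limitations concedes the cohort design. For a purely descriptive question an unadjusted ratio is a legitimate answer. This is correct, and the documents do not support saying that the ratio will be presented as a causal effect. But the plan does not call the contrast descriptive either.

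A third reply concerns mChoice. A reader might infer that an adjusted mChoice result and an unadjusted EPICC result on the same question would conflict. That does not hold. The mChoice propensity score serves a pre-post difference-in-difference analysis, and its Cox model concerns time to regimen change. It has no matching hazard ratio for discontinuation or nonadherence. The mChoice text shows that the authors recognize the problem; it does not provide a result against which EPICC's would be compared.

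Finally, the size of any bias rests on assumed inputs. That also stands: a 10-point imbalance with a weak confounder gives only 1.04.

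**Conclusion.** The point holds in a limited form. EPICC plans Cox and frailty comparisons by self-selected regimen and names no control for that selection, while the same article plans one for mChoice regimen groups on the stated ground that regimen cannot be randomized. Carried out as written, the hazard ratio by regimen may reflect who chooses each regimen.

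Size and direction cannot be determined from the article. The range of roughly 1.04 to 1.7 (or its reciprocal) assumes no true regimen difference, a single binary confounder with a hazard ratio of 1.5 to 3, and imbalances of 10 to 50 points between regimen groups. The bias could be negligible or material. This should be settled before analysis, but it is not a demonstrated error in a result.

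**What to change.** In the EPICC Analysis Plan:

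1. State that the regimen contrast in the Cox and frailty models will be adjusted, by a propensity score or by baseline covariates. The variables already listed there are the natural set: site/region, ethnicity, HIV risk perception, substance use, PrEP experience and relationship status.
2. Treat regimen as time-varying where participants switch, so that person-time and events are counted under the regimen in use.
3. Report the unadjusted hazard ratio alongside, labelled as descriptive.
4. State that the oral versus CAB-LA nonadherence contrast remains limited by the different outcome definitions, whatever adjustment is used.

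No new data are needed. The cost is a few sentences in the plan, a little more analysis work, and slightly wider intervals where a regimen group is small.
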